The sectors (natural spaces) in which the outdoor sessions will be conducted have been validated by experts to guarantee their suitability for the treatment activities [40]. The geographical areas are Sant Genís Forest (coordinates N 41° 25.930 E 2° 8.237) and Les Escletxes del Papiol (coordinates N 41° 26.319 E 2° 1.101). The researchers conducted a proof of concept study ([name], [name], [name], and [name]) in these sectors to test the manualisation of procedures and to evaluate the suitability of the NAT-FM structure based on the testing of a series of representative sessions [41]. 

The protocol of the NAT-FM is the result of the consensus of the proposed instruments, of the moments of assessments corresponding to each phase of the treatment, and of the administration platforms used. The decision to combine different assessments (CSA+EMA) is motivated by the need for a strategy that could obtain more precise information about the dynamics of the variables to be evaluated and, in particular, could record the affective and cognitive impact of each activity, as well as its transfer to everyday life. The frequency of administration of the EMA has been established from analysing the results of a systematic review on the characteristics of its use in studies with patients with chronic pain [42]. 

The NAT-FM treatment will be carried out in a group-based format in groups made up of a maximum of 20 patients per session with a total of 12 weekly 2 h sessions (1 session per week). The sessions will be directed by the [name], who is a physiotherapist of the CSSU of Vall d’Hebron University Hospital and also a psychologist and sports technician with the required legal qualifications for conducting this activity.

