In addition, to assess the clinical significance of the improvement in the primary outcome (FIQR), we will classify participants into two categories (responders vs. non-responders to treatment), using the following criterion: ≥20% reduction in the pre–post FIQR total scores [60]. This classification will be used to compute the number needed to treat (NNT) in NAT-FM compared with TAU. Finally, we will examine whether the effect of NAT-FM on the primary outcome at post and at the 6 and 9-month follow-ups is mediated/moderated through pre–post changes in secondary measures and personal factor variables (age, years from diagnosis, severity), using a structural equation model. According to the proposal of Luciano et al. [60], change scores before and after NAT-FM treatment will be calculated for these variables, as well as change scores before follow-up for the outcome variables. The analysis of temporality will increase the possibility of drawing conclusions about causality relationships. In this process, the data of the patients of the treatment with the greatest participation in the intervention will be analysed, defining participation as a minimum of 75% attendance of the sessions (per protocol analysis). The Benjamini–Hochberg correction for multiple comparisons will be applied; a procedure to detect false findings designed to overcome the limitations of other common procedures [61].

Complementary analyses will be conducted. Firstly, EMA intrasession measurements obtained from the NAT-FM treatment group will be subjected to a 2 (pre vs. post) × 6 (type of activity) mixed-effects ANOVA for pain, fatigue, self-efficacy, stress, and affect in order to assess the short-term impact of the planned activities. Secondly, EMA between-session measurements obtained from both arms of the study will be analysed both on a time-domain (single regression linear model for each dependent variable) and a frequency-domain basis (spectral analysis for each dependent variable) in order to assess transfer of the treatment effects to daily life.

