**Classical Structural Assessment (CSA)**					
General information measures					
Sociodemographic information (age, education level, etc.)	X				
Clinical information (medical history, FM history, etc.)	X				
Measures of clinical features and screening					
SCID-I (depression module)	X				
Measures of primary outcome					
FIQR (functional status)	X	X	X	X	X
Measures of secondary outcomes					
PANAS (negative and positive affect)	X	X	X	X	X
CERQ (emotional regulation)	X	X	X	X	X
PPCS (perceived competence)	X	X	X	X	X
RSES (self-esteem)	X	X	X	X	X
PCS (catastrophising)	X	X	X	X	X
PSS-4 (stress)	X	X	X	X	X
Measures of additional secondary outcomes					
HADS (anxiety and depression)	X	X	X	X	X
PIPS (psychological inflexibility)	X	X	X	X	X
TSK-11 (kinesiophobia)	X	X	X	X	X
SF-36 (physical function)	X	X	X	X	X
UKK (functionality)	X	X	X	X	X
AEAC (adverse effects) *			X		
PGIC/PSIC (impression of change) *			X		

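### The 75%-attendance rule takes the randomised comparison out of the mediation model, and for the post-treatment outcome alone mediator and FIQR change are concurrent

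*Protocol article*

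**What the plan says.** Objective (c), in the Introduction, is to identify mediators and moderators of the efficacy of NAT-FM. Section 2.6 turns this into an analysis of "whether the effect of NAT-FM on the primary outcome at post and at the 6 and 9-month follow-ups is mediated/moderated". The candidate variables are the secondary measures, each as its change over the treatment period, together with three personal factors: age, time since diagnosis and severity. Mediator change is therefore taken from baseline to end of treatment, and the outcome is FIQR at three times: post, 6 months and 9 months.

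The same paragraph makes two further statements about this step:

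- On causality: "The analysis of temporality will increase the possibility of drawing conclusions about causality relationships".
- On the patients used: "the data of the patients of the treatment with the greatest participation in the intervention will be analysed", with the cut-off given as "defining participation as a minimum of 75% attendance of the sessions (per protocol analysis".

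Section 2.4.1 sets the programme at "a total of 12 weekly 2 h sessions". The text does not say whether TAU patients stay in the model.

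Three other places matter. The primary between-group analysis in Section 2.6 is by intention to treat in both arms. Section 2.3 and Table 3 schedule an assessment after session 6 that includes FIQR and all the secondary questionnaires, and Section 2.5.1 applies these to both arms. The Discussion plans a separate sensitivity analysis of adherence.

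**The concern.** The quantity to be explained is the effect of NAT-FM compared with TAU. Randomisation protects that effect only while the groups stay as allocated. A patient can meet the attendance rule only if allocated to NAT-FM, and meets it through behaviour after allocation that may depend on prognosis, early response or tolerance. A model built on that set no longer decomposes the randomised effect.

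The second issue is time order. A mediator should change before the outcome it is said to affect. For the post outcome, the mediator change and the FIQR change start and end at the same visits. A patient whose FIQR falls for any reason may also report less catastrophising at that visit, and the model cannot tell which came first.

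What is at stake is the answer to objective (c). Selected, concurrent associations could be published as mechanisms of a treatment effect.

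**Working it through.** **1. The plan's own figure.** The mediation step has no figure of its own. The planning effect serves below as a yardstick, so it was checked first. With g = 0.50, 80% power and alpha 0.05 (two-sided assumed), the normal approximation gives 2 × (1.96 + 0.84)² / 0.50² ≈ 63 per arm, and 63 / 0.80 = 79 after rounding up. The t-test version gives 64 per arm, and 64 / 0.80 = 80. The stated 80 per arm reproduces.

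**2. The attendance rule.** 0.75 × 12 = 9 sessions. TAU patients have no sessions, so the rule cannot be applied to them. Two readings remain.

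- *NAT-FM attenders only.* Allocation is the same for every patient in the model. The path from treatment to mediator and the total effect on FIQR are both differences between arms, and neither can be estimated. Only a correlation between two changes in treated patients is left.
- *NAT-FM attenders against all TAU.* The arms differ by selection as well as by treatment.

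**3. Size of the selection under the second reading.** Assume no true effect, a normally distributed prognosis that correlates r with the tendency to attend, and a share p of NAT-FM patients reaching 9 sessions. The attenders' mean prognosis then differs from that of TAU by r × φ(z) / p SD, where z is the normal quantile cutting off the top share p. The documents give neither r nor p; both are assumptions.

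| p | kept of 80 | φ(z)/p | r = 0.2 | r = 0.3 | r = 0.5 |
|---|---|---|---|---|---|
| 90% | 72 | 0.195 | 0.039 | 0.059 | 0.098 |
| 80% | 64 | 0.350 | 0.070 | 0.105 | 0.175 |
| 70% | 56 | 0.497 | 0.099 | 0.149 | 0.249 |
| 60% | 48 | 0.644 | 0.129 | 0.193 | 0.322 |

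A simulation agreed to within 0.003. At p = 80% and r = 0.3 the spurious difference is 0.105 SD, about a fifth of 0.50 (0.105 / 0.50 = 0.21). If r is 0 there is no bias; if patients who fare better stop coming, the sign reverses.

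**4. The intervals side by side.**

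| FIQR outcome | Mediator window | Mediator window closed before outcome is measured? |
|---|---|---|
| Post | pre to post | No, same visit |
| 6 months | pre to post | Yes |
| 9 months | pre to post | Yes |

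**5. What concurrency can do.** Assume that treatment improves FIQR by 0.5 SD, that FIQR improvement drives the mediator with path 0.5, and that the mediator has no effect on FIQR. Both randomised arms are in the model.

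- Treatment to mediator: a = 0.5 × 0.5 = 0.25.
- Mediator to FIQR within arm: b = 0.5, although the true value is 0.
- Apparent indirect effect: 0.25 × 0.5 = 0.125. Share of the total: 0.125 / 0.5 = 25%.

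For a follow-up outcome measured as change from baseline, let that change correlate ρ with the pre–post change within arm. The apparent indirect effect is 0.25 × 0.5ρ and the total is 0.5ρ, so the share is again 25%. With adjustment for post FIQR it falls to about 0% (simulated at ρ = 0.5 and 0.7). The later outcomes thus have a time order, but the order alone does not exclude reverse causation.

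**The case against.** Four points deserve weight.

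- *The article is condensed and does not say that TAU patients are excluded.* The stated target implies a contrast, and a full protocol could specify one. This stands as a caution against asserting that TAU is dropped. It does not rescue the rule, because keeping TAU still sets attenders against an unselected arm.
- *The set is labelled per protocol, and the Discussion has an adherence sensitivity analysis.* As a sensitivity set it would be unobjectionable. Section 2.6, however, names it as the data for this step and states no all-randomised version of the mediation model.
- *The temporality sentence is hedged and follows a remark about follow-up change scores.* A reader might infer that the whole mediation analysis lacks time order. The documents do not support that: at 6 and 9 months the mediator window has closed before FIQR is measured. The criticism is confined to the post outcome, which the plan lists without exempting it from the temporality argument.
- *This is a mechanism analysis.* That is right. The primary comparison is by intention to treat and is untouched.

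A reader might also infer that change during treatment will be used as a moderator, which would be invalid. The sentence can equally be read as giving the mediator role to the changes and the moderator role to age, years from diagnosis and severity, so no finding is made on that.

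**Conclusion.** The point holds in two parts of unequal weight.

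The main part rests on the text alone. The mediation step uses a set defined after randomisation by a criterion that only one arm can meet. On either reading of what happens to TAU, mediation of the NAT-FM effect cannot be estimated free of selection bias under the stated rule.

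The lesser part is that for the post outcome, and only there, mediator and FIQR change cover the same pre–post interval, so time order cannot support a causal conclusion.

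The sizes are illustrations, not forecasts. The 0.04 to 0.32 SD depends on an assumed 60 to 90% reaching 9 sessions and an assumed correlation of 0.2 to 0.5. The 25% depends on an assumed reverse path of 0.5 and has meaning only with both arms in the model. Neither should be quoted as the bias of this trial. The plan should be changed for objective (c); the sample size and the primary analysis need no change on this account.

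**What to change.** - **Population.** Fit the mediation model in all randomised patients of both arms (80 per arm planned; 64 per arm after the anticipated 20% dropout), with allocation as the exposure. Keep the set with at least 9 of 12 sessions as a sensitivity analysis only.
- **Post outcome.** Either use mediator change from baseline to session 6, adjusted for baseline and session-6 FIQR, or report the pre–post result as a concurrent association with no claim of time order. The session-6 FIQR adjustment is needed because FIQR may already have driven the mediator by then.
- **6- and 9-month outcomes.** Report pre–post mediator change with and without adjustment for post FIQR, and say what each means. The adjustment guards against reverse causation but removes any mediation that acts through post FIQR, so it changes the quantity estimated.

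The cost is analysis wording. No new visit or instrument is needed, since the session-6 measures are already scheduled in both arms. The price is that a shorter mediator window is likely to give less precise indirect effects.

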## Abstract

The study protocol of a prospective and randomized controlled trial for the assessment of the efficacy of nature activity therapy for people with Fibromyalgia (NAT-FM) is described. The primary outcome is the mean change from baseline in the Revised Fibromyalgia Impact Questionnaire (FIQR) score at post-treatment (12 weeks) and at 9 months of follow-up, and secondary outcomes are changes in the positive affect, negative affect, pain, fatigue, self-efficacy, catastrophising, and emotional regulation. A total of 160 patients with fibromyalgia will be divided into two arms: treatment-as-usual (TAU) and NAT-FM+TAU. Pre, during, post, +6, and +9 months assessments will be carried out, as well as an ecological momentary assessment (EMA) of intrasession and intersessions. Results will be subjected to a mixed group (NAT-FM+TAU vs. TAU) × phase (pre, post, +6 months, +9 months) general linear model. EMA intrasession measurements will be subjected to a 2 (pre vs. post) × 5 (type of activity) mixed-effects ANOVA. EMA between-session measurements obtained from both arms of the study will be analysed on both a time-domain and frequency-domain basis. Effect sizes and number needed to treat (NNT) will be computed. A mediation/moderation analysis will be conducted.

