#### 2.5.2. Ecological Momentary Assessment (EMA)

EMA is used to assess: (a) the specific short-term impact of each activity and (b) the transfer of the treatment effects to everyday life. Measurements during the sessions (intrasession assessment) will be taken before and after each activity in nature using an online form. Measurements of the daily records between sessions (intersession assessment) will be carried out through an app, in which patients will have to respond six times a day (twice in the morning, twice in the afternoon, and twice at night). Intersession instruments will be applied to patients in both the control group (TAU) and intervention group (TAU+NAT-FM). However, intrasession instruments will only be applied to patients in the intervention group (TAU+NAT-FM).

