##### Other Secondary Outcome Measurements

The Self-Assessment Manikin (SAM) [59] is used to assess the affective state of people. It consists of three blocks of diagrammed pictograms in a continuous line, representing the following three dimensions of the affective response: valence, arousal, and dominance. Each scale has a 9-point Likert response format. The total scores on each scale range from 1 to 9. Higher scores on valence indicate greater positive mood; higher scores on arousal indicate greater activation and alertness; whilst for dominance a higher score indicates greater perception of control and personal confidence. These three dimensions of the affective response were evaluated both in intrasession assessment and in intersession assessment.

Single-item questionnaires: For the assessments of the variables fatigue, pain, and sleep quality, the three items of the Visual Analog Scale (VAS) of the FIQR were selected. For stress and self-efficacy, ad hoc questions were designed with a single item, rated on a scale from 0 to 10, in a VAS format. Higher scores indicate greater perceived fatigue, pain, sleep quality, stress, and self-efficacy. The variables fatigue, pain, and sleep quality were evaluated by intersession assessment, whereas the variables energy, pain, stress, and self-efficacy were evaluated by intrasession assessment.

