## Figures and Tables

**Figure 1 ijerph-17-00634-f001:**
[figure not shown]
Flow chart of the randomized controlled trial (RCT).

**Table 1 ijerph-17-00634-t001:** Structure of the Nature Activity Therapy for people with Fibromyalgia (NAT-FM), indicating the activities to be performed and the psychological targets to be addressed in each of the sessions.

Session	Activities					Targets					
	NW	YO	HK *	PH	SY **	Negative Affect	Positive Affect	Pain/Fatigue	Emotional Regulation	Self-Efficacy	Catastrophising
1			X					1–16			
2		X	X				1–6	1–2			
3		X	X	X				3–4		1–6	
4	X		X					5–6		7–10	
5	X		X	X				7–8			
6	X	X	X			1–6		9–10			
7	X		X		X			11–12			1–6
8	X		X	X				13–14	1–5		
9		X	X					15–16	6–8		
10			X	X		Family session					
11	X		X		X	1–6			1–8		1–6
12	X		X				1–6			1–10	

Note. The “X” expresses the sessions in which each activity is planned. The numbers of the targets’ columns are referred to the steps described on Table 2. Cognitive behavioural intervention on primary and secondary outcomes is distributed along the sessions. * Hiking is a homework assignment to do as a therapeutic exercise with cognitive targets. ** Shinrin Yoku is understood as mindfulness in a natural context. Nordic walking (NW); yoga (YO); hiking (HK); photography (PH); Shinrin Yoku (SY).

**Table 2 ijerph-17-00634-t002:** Steps in pain neuroscience education and in the cognitive-behavioural treatment for each outcome.

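### The between-arm intersession EMA regression makes no provision for repeated ratings within a patient; the activity factor and the sleep item's direction also need reconciling

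*Protocol article*

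**What the plan says.** **Intersession EMA.** Section 2.5.2 states that "patients will have to respond six times a day" through an app, in both arms. Section 2.6 lists two analyses of these data under complementary analyses, both meant to show whether treatment effects carry over to daily life. One is "time-domain (single regression linear model for each dependent variable"; the other is on a "frequency-domain basis (spectral analysis for each dependent variable". No patient effect, robust error or per-patient summary is mentioned for either.

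**Intrasession EMA.** The sentence before that in Section 2.6 specifies a "2 (pre vs. post) × 6 (type of activity) mixed-effects ANOVA" for the intervention arm. The Abstract gives the same analysis as a "2 (pre vs. post) × 5 (type of activity) mixed-effects ANOVA". Table 1 lists five activities: Nordic walking, yoga, hiking, photography and Shinrin Yoku. Its note adds: "Hiking is a homework assignment to do as a therapeutic exercise with cognitive targets".

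**Sleep item.** Section 2.5.2 (Other Secondary Outcome Measurements) takes the fatigue, pain and sleep items from the FIQR and states: "Higher scores indicate greater perceived fatigue, pain, sleep quality, stress, and self-efficacy". Section 2.5.1 (Primary Outcome Measure) says that a higher FIQR total means a worse state.

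**The concern.** Arm varies only between patients, so an arm comparison carries the information of 160 patients however many ratings each one gives. A linear regression with no patient term, run on the ratings themselves, takes every rating as new information and understates the standard error of the arm effect. Elsewhere the article names a repeated-measures structure where it wants one: a mixed-effects ANOVA for the FIQR and another for intrasession EMA. The most densely repeated data in the trial are the exception.

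At stake is the claim that benefit transfers to everyday life, which is one of the two stated uses of EMA. The Benjamini–Hochberg correction in Section 2.6 does not help, because it presupposes valid p-values.

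The other two points are simpler. A factor cannot have both five and six levels, and the direction of a sleep score must be settled before anyone interprets its sign.

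**Working it through.** **Inputs from the article.** Six prompts a day in both arms (Section 2.5.2); 12 weekly sessions (Section 2.4.1); alpha 0.05, power 0.80, g = 0.50, 20% dropout and 80 patients per arm (Section 2.2). Two-sided testing is assumed.

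**The plan's own figure.** The article gives no EMA error rate or ICC, so the only figure to reproduce is the sample size. n = 2 × (1.96 + 0.84)² / 0.50² ≈ 63 per arm (64 with the t-test). Dividing by 0.80 gives 79 or 80, so the stated 80 is reproduced. The simulations below use 64 and 80 per arm.

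**Ratings per patient (m).** The number of EMA days is not stated. Section 2.6 says only that EMA takes place during treatment, and Table 3 marks it only in the Session 6 column. Section 2.3 describes a day log between sessions. The assumed range is:
- one week: 6 × 7 = 42, or 6 × 6 = 36 without the session day
- twelve weeks: 6 × 7 × 12 = 504, or 6 × 6 × 12 = 432 without session days
- the 11 intervals between 12 sessions: 6 × 7 × 11 = 462, inside the range

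**Arm effect, ordinary least squares on individual ratings.** Design effect DE = 1 + (m − 1) × ICC. Actual type I error = 2 × [1 − Φ(1.96/√DE)]. The ICC is assumed.

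| m | ICC 0.1 | ICC 0.3 | ICC 0.5 |
|---|---|---|---|
| 36 | DE 4.5, 36% | DE 11.5, 56% | DE 18.5, 65% |
| 42 | DE 5.1, 39% | DE 13.3, 59% | DE 21.5, 67% |
| 432 | DE 44.1, 77% | DE 130.3, 86% | DE 216.5, 89% |
| 504 | DE 51.3, 78% | DE 151.9, 87% | DE 252.5, 90% |

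First cell: 1 + 35 × 0.1 = 4.5; 1.96/√4.5 = 0.92; error 36%. Last cell: 1 + 503 × 0.5 = 252.5; 1.96/√252.5 = 0.12; error 90%. The error passes 50% above an ICC of about 0.015 at m = 504, but only above 0.18 at m = 42 and 0.21 at m = 36.

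Null simulation with 64 per arm and a random intercept only agrees: 36%, 60% and 69% at m = 42 (500 runs each), and 76%, 87% and 90% at m = 504 (300 runs each).

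**Arm-by-time effect, same regression, simulated.**

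| Correlation in the data | m = 42 | m = 504 |
|---|---|---|
| Patient intercept only | 1% to 4% | 0% to 4% |
| Plus AR(1) errors of 0.5 | 8% to 23% | 13% to 27% |
| Plus patient slopes, SD 0.5 | 11% to 16% | 52% to 59% |

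The slope SD is in units of the rating SD (before slopes are added) over the whole EMA period. With an intercept only, the test is conservative, because between-patient variance inflates the residual but does not enter the time contrast.

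**One summary per patient.** A t-test on patient means or slopes gave about 5% in the same simulations (2% to 8% across scenarios). At 300 runs the simulation error around 5% is √(0.05 × 0.95/300) = 1.3 percentage points.

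**Activity factor.** The Abstract has 5 levels (4 degrees of freedom for activity), Section 2.6 has 6 levels (5 degrees of freedom), and Table 1 lists five activities. Nothing in the article supplies a sixth.

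**Sleep item.** The item is taken from an instrument whose total rises with deterioration, yet the EMA coding says that higher is better sleep. The article does not show the item's anchors.

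**The case against.** The best defence is that this is one line in a journal article about a complementary analysis. It does not say that individual ratings are the unit or that they are treated as independent, nor which term carries the arm comparison. Regression on patient means or slopes fits the wording and holds its level. Pairing it with spectral analysis, which usually works on each patient's own series, makes a per-patient reading plausible. That stands, and it is why the error rates above are conditional. It does not remove the point: a model is named, it has no patient term, and the sentence before shows the structure being named where it was intended.

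A reader might infer more than the article supports:
- *That most null comparisons would come out significant.* This depends on the ICC, the number of ratings and the term tested. One EMA week at ICC 0.1 gives 36% to 39%, and an arm-by-time test can fall below 5%.
- *That each patient gives hundreds of ratings.* The number of EMA days is not stated, and Table 3 is compatible with a single week.
- *That this regression is the only test of transfer to daily life.* The spectral analysis has the same purpose.
- *That the sleep result will have the wrong sign.* Section 2.5.1 gives the direction of the FIQR total, not of the sleep item. If the app item is anchored so that higher means better sleep, nothing reverses.
- *That only four activities are done in session.* The Table 1 note calls hiking homework, but the table marks hiking in all 12 sessions and as the only activity in session 1. The article does not settle the count.

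**Conclusion.** The point holds in conditional form. The named between-arm regression makes no provision for within-patient correlation. Fitted to individual ratings, its arm test would have a type I error of about 36% to 90% for an assumed ICC of 0.1 to 0.5 and 36 to 504 ratings per patient. An arm-by-time test could run from below 5% to about 59%, depending on serial correlation and on how much patients differ in slope. Fewer than 36 returned ratings would inflate the error less. Fitted to one summary per patient, the test would be sound.

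The five-versus-six contradiction in the activity factor needs no assumption. The sleep item is an inconsistency to be reconciled, not a demonstrated error of sign. All three affect complementary EMA analyses and leave the FIQR primary analysis untouched. They should be corrected before the EMA data are analysed.

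**What to change.** - **Intersession EMA.** State the number of EMA days, the unit of analysis and the term that carries the arm comparison. Then replace the single regression with a mixed model with patient as the cluster: at least a random patient intercept, plus a random time slope if arm-by-time is tested. Alternatively, compare one mean or slope per patient between arms, the option checked by simulation above.
- **Activity factor.** Use the activities actually rated in session as the levels, say how hiking is handled, and make the Abstract, Section 2.6 and Table 1 agree.
- **Sleep item.** Before analysis, state the anchors used in the app and the direction of scoring, and reconcile Sections 2.5.1 and 2.5.2.

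The cost is analysis wording only. SPSS and Mplus are already named and can fit these models, and no data collection changes. The downside is wider intervals for the EMA arm comparison.
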